### Measures (Table 1)

Measurements will take place at baseline and after 6 and 12 months of follow-up in patients, clinicians and family members or friends of the patients. All questionnaires are available in Dutch. At baseline, demographics, illness history and current characteristics of bipolar disorder will be recorded with the Questionnaire for Bipolar Illness (QBP-NL), that has been used previously in a large naturalistic cohort study [29,30]. We will measure overall functioning with the Functioning Assessment Short Test (FAST-NL-P). This questionnaire has been shown to have good psychometric proportions [31]. The current severity of the disorder will be measured with the Clinical Global Impression for Bipolar Disorder (CGI-BP) [32], rating manic and depressive symptoms separately, as well as the overall severity of bipolar disorder. Symptoms will be assessed with the Brief Symptom Inventory (BSI), which is the short version of the SCL-90 [33] and shows good psychometric proportions. Patients will fill in the BSI, which takes about 10 minutes to complete. Depressive symptoms will be measured with the Quick Inventory for Depressive Symptoms (QIDS-SR), a 16-item self report scale with excellent psychometric proportions [11]. Manic symptoms will be assessed with the Altman Self Rating Mania Scale (ASRM), which has shown satisfying psychometric qualities [34]. Course of illness and recurrences of mood episodes will be assessed with the Life Chart Method [35] during a telephone interview by a research assistant [36]. Quality of life will be assessed with the World Health Organisation Quality of Life -short version (WHOQoL-Bref), a widely used instrument with good psychometric proportions [37]. Assessment of needs will be measured by the CANSAS-P [38], of which validity and reliability proved to be satisfying [39,40]. Mastery will be measured with the Sense of Mastery Scale, which is widely used and is found valid and reliable [41]. Satisfaction with care will be measured with a Visual Analogue Scale (VAS), and costs with the TiC-P [42]. Information on Attitude on Drugs will be gathered with the Drugs Attitude Inventory (DAI-10) [43], which has been proved valid. Burden perceived by caregivers will be assessed with the Involvement Evaluation Questionnaire (IEQ), a self report list which is widely used and has been found valid [44]. Caregivers will also be asked to score satisfaction with care on a Visual Analogue Scale (VAS).

**Table 1 T1:** Measures in experimental group as well as in control group

Instrument	Filled in by	T0	T6	T12
QBP-NL	p/c	X		

CGI-BP	C	X	x	X

BSI	P	X	x	X

IDS-SR	P	X	x	X

ASRM	P	X	x	X

LIFE	P	X	x	X

FAST	P	X	x	X

WHOQoL-bref	P	X	x	X

CANSAS	P	X	x	X

Mastery	P	X	x	X

TIC-P	P	X	x	X

DAI-10	P	X	x	X

IEQ	F	X	x	X

VAS	p/f	X	x	X

P = patient; F = family or friend (informal caregiver); C = Clinician or professional caregiver (psychiatrist or psychologist)

### Statistical analysis

Primary outcomes are psychosocial functioning; course, prevalence and severity of psychiatric symptoms and quality of life.

Data will be analyzed according to the intention to treat-principle. Baseline comparability of the experimental and control groups in demographic and clinical variables will be evaluated with ANOVA/independent samples t-test and Chi-square tests. Differences in outcome between CC and CAU will be evaluated by means of (mixed model) analysis of covariance. A group*time-interaction term will be entered into the model to test for a difference in treatment effect over time. In analyzing a specific outcome variable, the baseline score of that variable will be used as covariate. The analysis will be extended using multilevel analysis that takes the nesting of measurements into account. In the multilevel analyses we consider location as the first level, patient as the second level, and the three measurements as a third level, using the principles of Twisk [45]. Finally we will take into account to what extent patients were exposed to the intervention by analysing the dose-effect relationship.

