## Methods/design

### Design

A pragmatic two-armed cluster randomized controlled trial (RCT) will be carried out in mental health outpatient clinics in the Netherlands. A Collaborative Care program will be executed in the experimental condition, whereas the control condition will continue to deliver Care as Usual (CAU). CC will be performed by the CC-team, with mental health nurses in a coordinating role. Baseline measurements will be obtained at inclusion and follow-up measurements will take place at 6 months and 12 months. The primary outcome measures are psychosocial functioning, symptoms, and quality of life. Secondary outcome measures are mastery, attitude towards medication and satisfaction with care. Family members or friends of patients will be asked to fill in questionnaires regarding perceived burden and satisfaction with care.

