### Power calculation

The power calculation concerns the comparison at T12 compared to T0 between the two groups (CC vs. CAU). We were not able to detect studies sufficiently comparable to ours to find a basis for estimating an effect size. We assume the effect size Cohen's d = 0,5, because we consider this a clinically relevant effect. Setting α < .05 (two-tailed), and the power (1-β) = .80, the required sample size is 2 × 63 patients. In cases of clustered randomisation the standard is to add 25% to this amount (n = 2 × 79). Taking into account an expected loss of 30%, a sample of 103 patients in each group is needed.

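### Three unranked primary domains, served by seven instruments, share one alpha of .05 and a sample size for one unnamed comparison, with no rule for what counts as success

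*Protocol article*

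**What the plan says.** The Design section of the protocol article states: "The primary outcome measures are psychosocial functioning, symptoms, and quality of life". The Statistical analysis section repeats the three domains and widens the second: "Primary outcomes are psychosocial functioning; course, prevalence and severity of psychiatric symptoms and quality of life". The Abstract gives the same three. None of these places ranks them or names an instrument.

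The Measures section links instruments to domains:

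- Functioning: "We will measure overall functioning with the Functioning Assessment Short Test (FAST-NL-P"), the only instrument given for it.
- Symptoms: the CGI-BP, "rating manic and depressive symptoms separately, as well as the overall severity of bipolar disorder"; the BSI ("Symptoms will be assessed with the Brief Symptom Inventory (BSI")); the QIDS-SR ("Depressive symptoms will be measured with the Quick Inventory for Depressive Symptoms (QIDS-SR")); the ASRM for mania; and the Life Chart for course and recurrence.
- Quality of life: the WHOQoL-Bref alone.

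All seven are scheduled at baseline, 6 and 12 months. Table 1 lists the depression scale as IDS-SR, whereas the text describes a "Quick Inventory for Depressive Symptoms (QIDS-SR), a 16-item self report scale".

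The Statistical analysis section describes a mixed-model analysis of covariance for each outcome variable, with that variable's baseline as covariate and a group-by-time term. It gives no significance level and no success rule. The only alpha is in the Power calculation section ("Setting α < .05 (two-tailed")), for one comparison of 12 months with baseline on an outcome that is not named.

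**The concern.** A primary outcome defines the claim the trial will make and the quantity its sample size protects. Here the plan separates primary from secondary outcomes but stops at the level of domains. For symptoms, five instruments could each carry the claim, and the CGI-BP alone yields three ratings. Nothing says whether one, some or all domains must show a difference.

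The choice could decide the result. The Background reports that all three earlier research programmes found improvement in manic but not depressive symptoms, and this trial adds a component aimed at depression. A mania scale, a depression scale and a general symptom inventory may therefore disagree, and the text leaves open which one counts. Protection from bias also differs: the only outcome assessor described as blind is the Life Chart interviewer.

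At stake is what the stated alpha of .05 and power of 80% refer to. Each can be read as a property of one comparison. Without a decision rule, they cannot both be claimed for the trial as a whole.

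**Working it through.** **Inputs.** From the Power calculation section: d = 0.5, two-sided alpha 0.05, power 0.80, 63 per arm, 25% added for clustering (79), 30% expected loss (103). From the Measures section: three domains and seven instruments. The document gives no correlations between outcomes, so these are assumptions, shown as a range.

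**1. The plan's own figure.** n per arm = 2 × ((1.960 + 0.842)/0.5)² = 62.8, so 63. Then 63 × 1.25 = 78.75, so 79, and 79 × 1.30 = 102.7, so 103. The stated numbers reproduce, for a single test at 5%.

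**2. If any one significant result suffices.** With each of k outcomes tested at 0.05 and independent, the family-wise error is 1 − 0.95^k. For k = 3 this is 1 − 0.857 = 14.3%; for k = 7 it is 1 − 0.698 = 30.2%. For equally correlated test statistics (correlation ρ, c = 1.960) the error is 1 − ∫ [Φ((c − √ρ·x)/√(1−ρ)) − Φ((−c − √ρ·x)/√(1−ρ))]^k φ(x) dx, evaluated numerically:

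| Outcomes tested | ρ = 0 | ρ = 0.5 | ρ = 0.8 |
|---|---|---|---|
| 3 (one per domain) | 14.3% | 12.5% | 9.8% |
| 7 (every instrument) | 30.2% | 23.0% | 14.9% |

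**3. If all three domains must succeed.** Alpha stays at or below 5%, but power falls. Taking the stated 80% for each test, joint power is 0.8³ = 51% if independent, 61% at ρ = 0.5 and 69% at ρ = 0.8.

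**4. If alpha is divided over three outcomes.** At 0.05/3 = 0.0167 the critical value is 2.394. The base size becomes 2 × ((2.394 + 0.842)/0.5)² = 83.8, so 84 per arm. With the document's own steps, 84 × 1.25 = 105 and 105 × 1.30 = 136.5, so 137 per arm, against 103 stated.

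Power per outcome at this level, which is also the first step of Holm's procedure:

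- At 63 effective per arm: Φ(0.5 × √(63/2) − 2.394) = Φ(0.412) = 66%.
- At the effective size the document's steps leave, 103 × 0.70 = 72.1 retained and 72.1/1.25 = 57.7: Φ(0.5 × √(57.7/2) − 2.394) = Φ(0.291), about 61%.

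**5. If one named outcome is tested first at 5%.** Alpha of .05 and the base size of 63 both stand for that test, with no change to the stated calculation.

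**The case against.** The strongest reply is that the plan does not say what a hostile reading puts into it. Four parts of that reply deserve weight.

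- **Test level.** A reader might infer that every outcome is tested at 5%. The Statistical analysis section gives no level; .05 appears only as an input to the sample size. This stands, so the error rates above are conditional.
- **Success rule.** A reader might infer that any one significant result supports the claim, and hence that alpha is simply not controlled. No such rule is written, and research question A asks about each domain without defining an overall win. This also stands: the inflation follows only under that rule.
- **Time points.** A reader might count separate tests at 6 and 12 months and double the number of tests. The plan describes one mixed model per outcome with a group-by-time term, and the power calculation singles out 12 months. Separate tests at each visit are not in the document, so seven is the better supported count. What stays open is whether the 12-month contrast or the interaction decides.
- **Scope.** Functioning and quality of life each already have one instrument, so the choice of instrument is open only for symptoms. The QIDS-SR/IDS-SR difference may be only a label, since Table 1 shortens other names too; it needs reconciling but carries little of the weight here.

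It can also be said that the details of a multiplicity procedure belong in an analysis plan that is not shown. That is fair for the procedure. It does not cover the choice of primary endpoint, or the outcome the sample size is meant for. The protocol is the place for both, and this article addresses both but leaves them open.

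**Conclusion.** The point holds in conditional form. The plan names three unranked primary domains, leaves five candidates for one of them, and attaches a single alpha and sample size to a comparison whose outcome is not named.

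If any one result at 5% were enough, the chance of at least one false positive primary finding would be about 10-14% for three outcomes and 15-30% for seven. If all three had to succeed, power would be about 51% to 61% for correlations of 0 to 0.5. These ranges rest on assumed equal correlations and, for the power figures, on the stated 80% per test. The document does not support an unconditional statement that the 5% level fails. It does support the statement that, as long as the rule is open, 5% error and 80% power cannot both be claimed for the trial's conclusion.

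**What to change.** Before data are unblinded, the sponsor should:

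1. name one symptom instrument as primary, with reasons;
2. state that 12 months is the decisive time point, and whether the 12-month contrast or the group-by-time term is the test;
3. test the three domains in a prespecified fixed sequence, each at 5%. FAST, then the named symptom scale, then WHOQoL-Bref is one example; the order is for the sponsor to choose and justify;
4. tie the sample size to the first test in the sequence;
5. label the remaining instruments and the 6-month results as secondary;
6. use one name for the depression scale in the Measures text and Table 1.

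This is a change of wording that leaves the base size of 63 per arm as it is. The downside is that a later domain can be claimed only if the earlier ones succeed.

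If the sponsor prefers not to order the domains, Holm's procedure over the three is an alternative. The plan should then state the lower first-step power: about 66% at 63 effective per arm, and about 61% at the roughly 58 that the document's own loss and clustering steps leave.

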### Power calculation

The power calculation concerns the comparison at T12 compared to T0 between the two groups (CC vs. CAU). We were not able to detect studies sufficiently comparable to ours to find a basis for estimating an effect size. We assume the effect size Cohen's d = 0,5, because we consider this a clinically relevant effect. Setting α < .05 (two-tailed), and the power (1-β) = .80, the required sample size is 2 × 63 patients. In cases of clustered randomisation the standard is to add 25% to this amount (n = 2 × 79). Taking into account an expected loss of 30%, a sample of 103 patients in each group is needed.

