### Randomisation

In this trial we will use clustered randomisation with outpatient clinic teams as clusters. Randomisation will be performed as follows: the CAU-study as well as the interviews with team members provide us with insight in the nature and intensity of CAU at that site. This enables us to describe CAU more precisely and formulate criteria for inclusion. Sites that meet the criteria for CAU will be invited to join in the CC-trial. Teams will be matched for characteristics of care offered to bipolar patients, as well as organisational characteristics such as team composition or type of organisation. One team of every pair will be randomly assigned to the experimental condition, and the other to the control condition. Patients in both teams who meet the inclusion criteria will be asked to participate in the study.

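### The flat 25% inflation for clustering leaves the stated 80% power dependent on a team size and intraclass correlation that the calculation does not use

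*Protocol article*

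**What the plan says.** The Randomisation section makes teams the unit of allocation: "we will use clustered randomisation with outpatient clinic teams as clusters". Teams are matched on the care they give and on organisational features, and one team of each pair is allocated to each arm.

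The Power calculation section starts from an individually randomised comparison. On the effect size: "We assume the effect size Cohen's d = 0,5, because we consider this a clinically relevant effect". On the resulting number: "Setting α < .05 (two-tailed), and the power (1-β) = .80, the required sample size is 2 × 63 patients". It then turns to clustering: "In cases of clustered randomisation the standard is to add 25% to this amount". This gives 79 per arm. The last step is for attrition: "Taking into account an expected loss of 30%, a sample of 103 patients in each group is needed".

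The article gives no number of teams, no patients per team, no intraclass correlation (ICC) and no source for the 25%. The Statistical analysis section plans the baseline score as a covariate and a multilevel model with location as a level. The power calculation uses neither.

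**The concern.** The loss of information from randomising teams depends on how many patients each team supplies and how alike patients within a team are. A rule that fixes the inflation at 25%, whatever these are, is not a standard method. It is right for one combination of team size and ICC and wrong for the others, in either direction.

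What is at stake is power. The planned multilevel analysis includes location, so clustering is addressed at the analysis stage. But recruitment could reach 103 per arm from a few large teams and look on target while power is well under 80%, and a null result might then be read as no effect of Collaborative Care. With many small teams, the same 25% could be enough or more than enough. The text gives no means of telling these cases apart.

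**Working it through.** **Inputs from the Power calculation section:** two-sided α = 0.05, power 0.80, d = 0.5, inflation 1.25, 79 analysed per arm. **Assumed, because the article gives neither:** k = 4, 6, 8, 12 or 16 teams per arm of equal size, and ICC 0.01 or 0.05.

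**1. Reproduce the plan's figures.** n per arm = 2 × (1.960 + 0.842)² / 0.5² = 62.8, so 63. Then 63 × 1.25 = 78.75, so 79. Both agree with the article.

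**2. Where is 1.25 the right factor?** The design effect is DE = 1 + (m − 1) × ICC, with m = 79/k. Setting DE = 1.25 gives ICC = 0.25/(m − 1).

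| Teams per arm (k) | Patients per team (m) | ICC at which DE = 1.25 |
|---|---|---|
| 4 | 19.75 | 0.25/18.75 = 0.013 |
| 6 | 13.17 | 0.25/12.17 = 0.021 |
| 8 | 9.88 | 0.25/8.88 = 0.028 |
| 12 | 6.58 | 0.25/5.58 = 0.045 |
| 16 | 4.94 | 0.25/3.94 = 0.063 |

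**3. Power with 79 analysed per arm, no baseline adjustment.** The effective number per arm is 79/DE, and the noncentrality is δ = 0.5 × √((79/DE)/2). Normal approximation: power = Φ(δ − 1.960). Allowing for few teams: noncentral t with noncentrality δ on 2k − 2 df.

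Example, k = 6 and ICC 0.05: DE = 1 + 12.17 × 0.05 = 1.61; 79/DE = 49.1; δ = 2.48. Power is 70% by normal approximation and 61% by t on 10 df.

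| k | ICC | DE | Power, normal | Power, t (df) |
|---|---|---|---|---|
| 4 | 0.01 | 1.19 | 82% | 67% (6) |
| 6 | 0.01 | 1.12 | 84% | 76% (10) |
| 8 | 0.01 | 1.09 | 85% | 80% (14) |
| 12 | 0.01 | 1.06 | 86% | 83% (22) |
| 4 | 0.05 | 1.94 | 62% | 47% (6) |
| 6 | 0.05 | 1.61 | 70% | 61% (10) |
| 8 | 0.05 | 1.44 | 74% | 68% (14) |
| 12 | 0.05 | 1.28 | 79% | 76% (22) |

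**4. Separate the two causes.** The normal column shows the effect of the inflation factor alone. At ICC 0.01 every DE is below 1.25, so the 25% is generous there, and the 67% with 4 teams comes wholly from having 6 df. At ICC 0.05 the step from normal to t costs 61.7 − 47.4 = 14.3 points with 4 teams and 79.3 − 75.7 = 3.6 points with 12. The rest of the shortfall is due to the factor.

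**5. Effect of the planned covariate.** If the baseline–outcome correlation were 0.5 (assumed) and the ICC stayed at 0.05, δ is multiplied by 1/√(1 − 0.25) = 1.155. Power by t on 2k − 2 df is then 59%, 73%, 80% and 87% for 4, 6, 8 and 12 teams per arm.

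**The case against.** The strongest reply has four parts.

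- **This is a condensed article.** Team numbers may stand in a fuller protocol, so their absence alone is no fault. That stands. But the article states its rule in full, calls it the standard and derives 79 from it. The rule itself is what is wrong.
- **The shortfall rests on assumptions.** A reader might infer that 80% power holds only for a very small ICC, or that true power is about 50–70%. The documents support neither. With about 5 patients per team, 1.25 covers an ICC up to 0.063, and the assumed cases span 47% to 86% depending on method. Part of the drop in the t figures comes from the few degrees of freedom and not from the 25%.
- **A large ICC is not shown.** One might argue from the remark in the Study on Care as Usual section that usual care varies considerably among clinics. That describes clinics nationally. The same section restricts entry to clinics whose care does not already resemble the intervention, and the Randomisation section matches teams. Both steps may reduce between-team differences, and variation in care delivery is not the ICC of a patient-reported outcome.
- **The planned analysis may do better.** The baseline covariate could recover part of the loss: with 8 or more teams per arm, step 5 reaches 80% at ICC 0.05. With 4 or 6 it does not, and the power calculation claims no such credit. The 2k − 2 df also ignore the matched pairs; a pair-based analysis would have different df.

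**Conclusion.** The point holds as an invalid rule in the power calculation. The 80% is not wrong for every plausible design, but nothing in the calculation supports it, because it depends on a team size and an ICC that were not used. Under the assumptions in the working, the flat 25% is more than enough at ICC 0.01. At ICC 0.05 it falls short by normal approximation for 4 to 12 teams per arm (62% to 79%), and further short once the small number of teams is allowed for (47% to 76%).

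Confidence is high for the error in the rule and much lower for the size of any loss, which rests wholly on assumed team numbers, ICC and equal team sizes, with no baseline adjustment. The figures also take 79 analysed per arm as given. In fact 103 is 79 × 1.30 = 102.7 rounded up, and a 30% loss from 103 leaves 103 × 0.70 = 72, so power would be somewhat lower on that separate count. The paragraph should be corrected; the trial is not invalidated by it.

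**What to change.** Delete the statement that 25% is the standard. Give the planned number of teams per arm and patients per team, compute the design effect as 1 + (m − 1) × ICC, and restate power at the same total N over an ICC range such as 0.01 to 0.05. Use team-level degrees of freedom that match the analysis, paired or unpaired. If credit is wanted for the baseline covariate, state the assumed correlation and show the gain explicitly.

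The cost is a rewritten paragraph and probably a less favourable power figure. Restating needs no extra patients. A cap on patients per team would help the achieved design effect match the planned one, but it is an optional recruitment choice.

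### The 30% loss allowance is applied as 79 × 1.3 instead of 79 / 0.7, so 103 patients per group gives about 76% power, not the stated 80%

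*Protocol article*

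**What the plan says.** The whole calculation stands in one paragraph, under Power calculation in the protocol article. It concerns the difference between the two arms from baseline to 12 months. The steps are:

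- Effect size: "We assume the effect size Cohen's d = 0,5, because we consider this a clinically relevant effect".
- Unclustered sample size: "Setting α < .05 (two-tailed), and the power (1-β) = .80, the required sample size is 2 × 63 patients".
- Clustering: "In cases of clustered randomisation the standard is to add 25% to this amount", which the paragraph carries through to 79 per group.
- Attrition: "Taking into account an expected loss of 30%, a sample of 103 patients in each group is needed".

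Allocation is 1:1 by matched pairs of teams. The Randomisation section says: "One team of every pair will be randomly assigned to the experimental condition, and the other to the control condition". The article gives no other recruitment target.

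**The concern.** The last step does not follow from the one before it. If 79 patients per group must remain and 30% of those enrolled are expected to be lost, 103 enrolled is too few. The three printed figures (79 needed, 30% lost, 103 enrolled) cannot all hold. The number matches the common slip of adding 30% to the required sample instead of dividing by the retained fraction.

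What is at stake is the only operating characteristic claimed for the sample size. If loss is as expected, the trial runs at lower power than stated. The paragraph itself says that no comparable study was found on which to base the effect size, and the Discussion warns that taking part in the study may narrow the contrast between the arms. An avoidable loss of power adds to both.

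**Working it through.** **Inputs, all from the Power calculation section:** d = 0.5 (SD = 1), two-sided α = 0.05, power 0.80, cluster inflation 1.25, expected loss 30%. Allocation is 1:1.

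**Reproducing the plan's figures**

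1. Unclustered: n = 2(1.960 + 0.842)² / 0.5² = 62.8, so 63 per group, as printed.
2. Clustering: 63 × 1.25 = 78.75, so 79 per group, as printed.
3. Attrition: 79 × 1.30 = 102.7, so 103 per group, as printed.

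Other plausible routes do not give 103:

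| Route | Result per group |
|---|---|
| 79 / 0.70 | 112.9 |
| (63 / 0.70) × 1.25 | 112.5 |
| 63 × 1.55 (both allowances added) | 97.7 |
| 63 / 0.75 / 0.70 | 120 |

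**What 103 per group delivers**

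- Remaining at 12 months: 103 × 0.70 = 72.1, about 72, against 79 required.
- Effective n after the plan's own cluster inflation: 72 / 1.25 = 57.6 per group.
- Power (normal approximation): Φ(0.5 × √(57.6 / 2) − 1.960) = Φ(0.72) = 76.5%. The same formula gives 80.3% at 79 per group (effective n 63.2).
- Power (t-test): 75.8%, against 79.6% at 79 per group.
- Loss that 103 can absorb: 1 − 79 / 103 = 23.3%.

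**What a 30% loss requires**

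- 79 / (1 − 0.30) = 112.9, so 113 per group, or 226 in total against 206.
- Check: 113 × 0.70 = 79.1. The effective n is 63.3 and power is 80.3% (normal approximation).

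**Sensitivity to the cluster inflation.** The 1.25 factor was held fixed above. Smaller clusters have a smaller design effect. As an assumption, suppose a fixed intracluster correlation and a factor of 1.25 at 79 per group. At 72 the factor is then about 1 + 0.25 × 72 / 79 = 1.23, the effective n is about 58.6 and power is about 77%, still below 80%.

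**The case against.** The strongest counter-argument concerns the planned analysis, not the arithmetic. The Statistical analysis section specifies a mixed-model analysis of covariance with the baseline score as covariate, and this can recover precision. To bring an effective n of 57.6 up to 63, the residual variance must fall to 57.6 / 63 = 0.914 of the value assumed.

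- If d is scaled by the SD of the 12-month score, adjustment multiplies the variance by 1 − ρ². That reaches 0.914 at a baseline-to-follow-up correlation of about 0.29.
- If d is scaled by the SD of the change score, the factor relative to a change-score analysis is (1 + ρ) / 2. That is at or below 0.914 for any ρ up to about 0.83.

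In addition, patients lost after the 6-month visit still contribute to a repeated-measures model, so 72 is the number with 12-month data, not the number in the analysis.

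Both points are fair, and the power of the analysis actually run may well reach 80%. Neither repairs the printed calculation. It takes no credit for covariate adjustment, and the article gives neither a correlation nor the timing of losses, so the gain cannot be quantified from it. If such a gain is relied on, it has to be stated.

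Two other defences are weaker. One reads the 30% as a surplus on top of completers. That would reproduce 103, but the text speaks of an expected loss, and on that reading the true allowance is 23%. The other notes that 72 exceeds 63. Ignoring clustering, 72 per group would indeed give about 85% power, but teams are randomised and the plan itself requires the cluster addition.

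It is also fair to say that the effect is small and that neither the estimate nor the type I error is affected.

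**Conclusion.** The concern holds. The first two steps of the calculation are correct. The third multiplies by 1.3 where it should divide by 0.7. Under the plan's stated assumptions (d = 0.5, two-sided 5%, a fixed 25% cluster inflation, 30% loss, no credit for covariate adjustment), 103 per group leaves about 72 patients with 12-month data instead of 79, and power is about 76% instead of 80%. The type II error rises from 20% to about 24%. The correctly computed enrolment is 113 per group.

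The size is modest, and more precision than about 76% is not warranted, because the 25% inflation is generic and the effect size is assumed. Whether 25% is enough for clustering is a separate question on which this conclusion does not depend.

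**What to change.** Correct the final sentence of the Power calculation section in one of two ways:

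- **Change the number:** with an expected loss of 30%, 113 patients per group (226 in total) are needed. This costs 20 more patients than the present 206.
- **Keep 103 per group and restate what it gives:** about 76% power at 30% loss, or 80% power if loss does not exceed 23%. This needs no extra patients.

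If the sponsor prefers to keep 103 and still claim 80% power because of the baseline-adjusted model, the paragraph should say so. It should give the assumed baseline-to-12-month correlation and say which SD the effect size of 0.5 refers to.
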